## Abstract

**Background:**

The individuals with tuberculosis (TB) experience a variety of barriers, needs, and challenges when receiving the treatment. Evidence on holistic patient-centered psychosocial interventions that promote self-efficacy and the ability to complete treatment-related tasks and goals is scarce in India.

**Objectives:**

To adapt an intervention aimed at strengthening the self-efficacy of individuals on TB treatment and their family caregivers, and to evaluate its effectiveness compared with the standard of care on the primary outcome of improved TB treatment self-efficacy and secondary outcomes of improved medication adherence, reduced TB-related stigma, and improved infection control practices.

**Methods:**

A multicentric hybrid Type I mixed method implementation research design will be used to adapt and evaluate the implementation feasibility and effectiveness of delivering a self-efficacy-based intervention under National Tuberculosis Elimination Program (NTEP) settings in India. A two-arm non-randomized cluster intervention design will be employed to evaluate the impact of a self-efficacy intervention, which includes individual counseling and peer group sessions (*n* = 240) in comparison to the standard of care (*n* = 240) on primary and secondary outcomes. Qualitative in-depth interviews and focus group discussions, guided by the Consolidated Framework for Implementation Research (CFIR), will be conducted to explore contextual factors influencing implementation.

**Discussion:**

The proposed study could generate evidence for a holistic and evidence-informed psycho-social intervention for individuals with TB and their family caregivers. It aims to improve their self-efficacy in overcoming TB treatment challenges and address the key psycho-social barriers comprehensively. Qualitative insights from the study are expected to guide/facilitate the pragmatic scale-up of self-efficacy-based interventions under the National TB program of India.

**Clinical trial registration:**

The study has been registered in the Clinical Trial Registry of India CTRI/2024/05/066847.

## Background

Individuals with tuberculosis (TB) experience a range of physical and psycho-social challenges (1). Active tuberculosis (TB) deteriorates both physical and mental health, while TB treatment-related difficulties include long treatment duration, medication side effects, tablet burden, poor adherence, stigma, financial limitations, and limited health system assistance, all of which contribute to treatment interruption and poor outcomes (2). Disease denial, fear of death, and perceived infection risk contribute to fear, emotional distress, and anxiety among patients and caregivers (3). At the time of diagnosis and during the early phase of treatment, patients often experience stigma, hopelessness, and even suicidal ideation. Consequently, adverse psycho-social and life experiences, such as anxiety, depression, tension, and low self-esteem, are further intensified by treatment burden, medication intolerance, physical deterioration, and other concerns encountered throughout the treatment course (4).

The mental health of individuals with TB and their caregivers is influenced by the perceived burden of treatment and concerns related to infection risk. The disease and treatment-associated challenges impose a substantial psycho-social and economic burden on family caregivers, who are themselves at risk of acquiring infection during the caregiving process. Multiple issues may potentially arise for individuals with tuberculosis (TB) and their caregivers during the treatment cascade, subsequently affecting treatment adherence and outcomes. A recent meta-analysis revealed that poor outcomes, such as mortality, loss to follow-up, and disease recurrence, are six times higher when more than 10% of doses are missed during TB therapy (5). While TB treatment and diagnosis are provided free of cost, the acceptability of TB services is limited due to the poor knowledge, attitude and practice of the community toward TB. Stigma and incorrect perceptions lead to poor health-seeking behavior, such as delayed treatment, inadequate infection prevention, and non-adherence, which contribute to the development of drug resistance (6, 7).

An effective intervention that significantly enhances the self-efficacy of individuals with TB in treatment management and infection prevention is essential for achieving the national TB elimination goals, including reducing transmission and increasing the treatment success rate. The ability of individuals with TB and their caregivers to cope with the multifaceted challenges they encounter daily largely depends on their level of self-efficacy. In India, there is a lack of evidence-based interventions aimed at enhancing/strengthening the self-efficacy of TB patients and their caregivers in the context of treatment uptake/adherence and infection prevention. Although the treatment efficacy among individuals with TB is generally low, no studies or interventions have been reported in India that specifically address treatment self-efficacy (8, 9). Currently, there is meager evidence on psycho-social interventions that are effective, acceptable, and scalable in improving treatment self-efficacy. Therefore, we propose a study to adapt and evaluate a self-efficacy-based intervention designed to support individuals with TB and their caregivers in strengthening their actions, behaviors, and self-management skills to effectively address the challenges and demands of TB disease and treatment.

## Primary objectives

To adapt and evaluate the self-efficacy-based intervention compared with the standard of care on the following outcomes:
• Primary outcomes: *improved TB treatment self-efficacy*.• Secondary outcomes: *(i) improved medication adherence (ii) reduced TB-related stigma and (iii) improved infection control self-management practices*.To evaluate the efficacy of a self-efficacy-based intervention, compared with the standard of care, on secondary outcomes among caregivers: *improved caregivers' self-efficacy, decreased TB-related stigma, and improved infection control self-management practices*.To assess the acceptability level among patients, caregivers, and health care providers.

## Hypothesis/research question

A self-efficacy-based intervention will be both clinically (*d* > 0.3) and statistically (*p* < 0.05) more effective in improving treatment self-efficacy among individuals with TB, as well as enhancing treatment adherence, infection control practices, and reducing TB-related stigma compared with the standard of care.

## Overall design

A hybrid mixed-method implementation design will be employed to evaluate the implementation acceptability and preliminary efficacy of delivering a self-efficacy-based intervention by front-line healthcare staff, family caregivers, and patient champions. The intervention aims to enhance treatment self-efficacy, mental health, and self-management practices related to infection control among individuals with TB and caregivers.

## Design for primary objective 1

A self-efficacy-based intervention manual and standard operating procedures were developed by adapting the findings from formative research conducted among individuals with TB, caregivers, and front-line healthcare staff. The PRODUCES framework (Problem, Objective and Design, End-Users, Co-creators, Evaluation, and Scalability) was used to guide the design and development of this implementation research study (10).

The self-efficacy drive intervention manual and standard operating procedures (SOPs) will be further adapted to align with the workflow of government TB care delivery systems at the proposed study sites (11).

## Design for primary objective 2

A two-arm, non-randomized cluster intervention study will be conducted to achieve this objective. The study population will include

Adult drug-sensitive (DS) TB patients (> 18 years) who have initiated TB treatment.Patients with low treatment self-efficacy (self-efficacy score of < 30 on the chronic diseases self–efficacy scale) (12).Adult drug-resistant (DR)-TB patients on a shorter treatment regimen.Caregivers of patients who meet criteria 1–3 above.

## Study sites

In the proposed research, individuals with tuberculosis (TB) will be enrolled in the National Tuberculosis Elimination Program (NTEP) facilities located in selected tuberculosis treatment units (TUs) across three districts in Tamil Nadu—Chennai, Kanchipuram, and Tiruvallur. Treatment initiation and follow-up will be carried out under the supervision of NTEP staff.

## Implementation

A prospective quantitative and qualitative evaluation of the proposed intervention will be conducted among individuals with TB aged 18 and above, including both males and females, who exhibit low treatment self-efficacy. The evaluation will assess the intervention's effects on treatment self-efficacy (primary outcome and secondary outcomes), including treatment adherence, intermediate mental and physical health outcomes, and infection control practices.

In accordance with a hybrid effectiveness-implementation design, longitudinal qualitative data will also be collected to triangulate with quantitative findings, thereby providing deeper insight into intervention mechanisms and contextual factors. The enhanced standard of care, comprising brief counseling and information, education, and communication (IEC) activities, will be compared to evaluate the added benefit of the self-efficacy-based intervention.

## Sample size

We estimated that our proposed intervention would reduce the proportion of individuals with poor self-efficacy from 50 to 35%, corresponding to an absolute difference of 15%. A sample size of 166 TB patients per arm (332 in total) was calculated assuming an average cluster size of 50, a significance level of α = 5%, β = 20% and a power 1–β = 80%.

Considering an average cluster size of 50, yielding a design effect of 1.5, we predict that we would require 500 participants, with five clusters in the control arm and five in the intervention arm. Accounting for an anticipated 10% dropout rate, we plan to screen and include approximately 547 participants overall. Arm wise sample size has been explained in Figure 1.

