**Figure 1 F1:**
[figure not shown]
Study arm description.

The sample size is calculated using the formula:

S = (zα + zβ) ∧ 2 ^*^ (C^*^(1–C) + I^*^(1–I)) / (C–I) ∧ 2, where C represents the expected proportion in the control arm and I represents the expected proportion of the intervention arms.

Participants will be screened based on their baseline self-efficacy score, and TB treatment facilities will be regarded as clusters. During the recruitment phase, the matching of average self-efficacy scores between the intervention and control clusters will be assessed. Recruitment within each cluster will continue until the required sample size per cluster is achieved. Eligible participants will be enrolled sequentially from the health centres within the designated selected TU.

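### The 80% power stated for 50% versus 35% uses normal quantiles; with five clusters per arm and the plan's own design effect, that comparison has about 69% on 8 degrees of freedom.

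*Protocol article*

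**What the plan says.** The Sample size section of the protocol article assumes that the intervention will "reduce the proportion of individuals with poor self-efficacy from 50 to 35" per cent, with "a significance level of α = 5%, β = 20% and a power 1–β = 80" per cent. It continues: "A sample size of 166 TB patients per arm (332 in total) was calculated assuming an average cluster size of 50". The next paragraph adds the clustering allowance, "Considering an average cluster size of 50, yielding a design effect of 1.5", and concludes that "we would require 500 participants, with five clusters in the control arm and five in the intervention arm". Allowing for 10% dropout, about 547 are to be included.

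The formula printed below Figure 1 is the two-proportion formula with unpooled variance. It uses normal quantiles and has no term for cluster size or number of clusters. The text below it says that "TB treatment facilities will be regarded as clusters". Under the design for primary objective 2, the study is a two-arm, non-randomized cluster intervention study.

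The section on analysis of study outcomes data plans linear mixed models for the continuous self-efficacy score, with arm, time and their interaction as fixed effects.

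**The concern.** A design effect corrects the variance for clustering. It does not correct for how few clusters there are to estimate that variance. Arm is a facility-level attribute here, so the arm comparison is judged against variation between facilities, and five per arm leave 8 degrees of freedom. Normal quantiles understate the critical value at that size, so the stated 80% is too high for the comparison it refers to.

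A reader of a null result would then take the risk of missing the planned 15-point difference as 20%, when for this comparison it is nearer 31%.

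Two smaller reporting points belong with this. Cluster size alone does not produce a design effect; an ICC is also needed, and none is given. And 166 per arm is described as assuming a cluster size of 50, although cluster size does not enter the formula.

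**Working it through.** **Inputs from the Sample size section.** C = 0.50, I = 0.35, alpha 5%, power 80%, cluster size m = 50, design effect (DE) 1.5, 500 participants, five clusters per arm, about 547 after the dropout allowance. Sidedness is not stated; two-sided reproduces the plan's figure (one-sided would give 131 per arm).

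**1. Reproduce the plan's figures.**
- S = (1.960 + 0.842)² × (0.50 × 0.50 + 0.35 × 0.65) / 0.15² = 166.6 per arm; the plan states 166, 332 in total.
- 332 × 1.5 = 498; the plan states 500, which is 5 + 5 clusters of 50.

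So 166 is the figure before any allowance for clustering.

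**2. Implied ICC.** DE = 1 + (m − 1) × ICC, so 1.5 = 1 + 49 × ICC and ICC = 0.5/49 = 0.0102.

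**3. Power on the plan's own basis.**
- Effective n per arm = 250/1.5 = 166.7
- Standard error = √(0.4775/166.7) = 0.0535
- Non-centrality = 0.15/0.0535 = 2.80
- Normal power = Φ(2.80 − 1.96) = 80.0%, as stated.

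**4. The same comparison with ten clusters.** Degrees of freedom = 2 × (5 − 1) = 8, critical value 2.306. The non-central t with non-centrality 2.80 gives 69.1%. A beta-binomial simulation of a cluster-level t-test (200,000 runs, five clusters of 50 per arm) gives 68.7%.

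**5. Keeping 1.96 does not restore the claim.** In the same simulation under no effect, the cluster-level test with critical value 1.96 has a type I error of about 8.6%. The stated 80% power and 5% alpha are therefore not met together.

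**6. Full retention of 547.** 273.5 per arm is 54.7 per cluster, so DE = 1 + 53.7 × 0.0102 = 1.548. Non-centrality is 2.885 and power on 8 degrees of freedom is 71.5%.

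**7. Detectable difference.** On 8 degrees of freedom, 80% power needs a non-centrality of 3.20, against 2.80 with normal quantiles. With 250 per arm and DE 1.5, that is a difference of 0.170, or 17 points from a control proportion of 50%.

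**8. Sensitivity to the ICC** (250 per arm, m = 50, 8 degrees of freedom). Only 0.0102 follows from the document; the other values are assumptions to show the range.

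| ICC | DE | Power, normal | Power, 8 df |
|---|---|---|---|
| 0.005 | 1.245 | 87% | 77% |
| 0.0102 | 1.50 | 80% | 69% |
| 0.02 | 1.98 | 68% | 57% |
| 0.03 | 2.47 | 59% | 48% |
| 0.05 | 3.45 | 46% | 37% |

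**The case against.** The strongest reply is that 69% belongs to a test the protocol does not plan. The planned analysis is a linear mixed model on the continuous score with three time points, and a continuous analysis uses more information than a dichotomy. If scores are normal (an assumption), moving from 50% to 35% below a cut-off is a shift of 0.385 SD. With 250 per arm and 8 degrees of freedom, non-centrality is 0.385/√(2 × DE/250). That gives 87% power at DE 1.5, and 81% at DE 1.78, the value if the implied ICC is read on the binary scale and converted to the latent scale (about 0.016). Stable differences between facilities also cancel from an arm-by-time contrast, so neither the ICC behind 1.5 nor the 8 degrees of freedom need carry over unchanged.

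This stands as a limit on the point. A reader might infer that the trial as designed has only 69% power for its primary analysis; the document does not support that. Nor does it support the opposite: at the effect size of 0.3 named in the hypothesis section, the same two calculations give 67% and 60%. The article gives neither an SD nor an ICC for the continuous score. The Sample size section claims its 80% for the binary difference, and that claim is what fails.

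It is also fair that inflating by a design effect with normal quantiles is a common planning method, and that the arithmetic is right on that method. The fault is applying a large-sample method to ten clusters. The unstated ICC and the wording around 166 are reporting points only: the ICC can be recovered from the figures given, its source may be in the full protocol, and the inflation is applied separately in the next paragraph.

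**Conclusion.** The point holds for the binary comparison used to size the trial. With five clusters of 50 per arm and a design effect of 1.5, power for 50% versus 35% is about 69%, not 80%, and about 72% if all 547 are retained. The difference detectable with 80% power is about 17 points.

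This rests on two-sided alpha of 5%, equal cluster sizes, 250 analysed per arm (except for the 547 figure), the implied ICC of 0.0102 and cluster-level inference on 8 degrees of freedom. The last is the standard choice for ten clusters in two arms and is not stated in the document. Unequal clusters or a larger ICC would lower the figure. Baseline adjustment could recover some power, but the Sample size section does not invoke it.

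The power of the planned mixed model is undetermined. This should be fixed; it does not by itself call the design or the planned analysis into question.

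**What to change.** In the Sample size section:

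- State the ICC of 0.0102 behind the design effect of 1.5, and its source.
- Describe 166 per arm as the figure before cluster inflation.
- Restate power for the binary sizing endpoint on a t reference with 8 degrees of freedom: about 69% for 15 points, or 80% for about 17 points. Add a range over assumed ICCs, for example 77% at 0.005, 57% at 0.02 and 37% at 0.05.
- Say that this is not the power of the planned linear mixed model on continuous scores. Give that power separately, with a small-sample degrees-of-freedom correction for ten clusters and stated SD and ICC assumptions.

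The cost is wording, one further power calculation and a less favourable stated power. No extra patients are needed and neither the design nor the analysis has to change.

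### The abstract's 240 per arm (480 in total) contradicts the sample-size section, which requires 500 and plans to include about 547; 480 is below the plan's own requirement even with no dropout

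*Protocol article*

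**What the plan says.** The Methods paragraph of the abstract describes the intervention as one "which includes individual counseling and peer group sessions (*n* = 240) in comparison to the standard of care (*n* = 240"), that is 480 participants in two equal arms. It does not say whether these are enrolled or analysed.

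The Sample size section builds its number in three steps:

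- The intervention is expected to "reduce the proportion of individuals with poor self-efficacy from 50 to 35%, corresponding to an absolute difference of 15" percentage points, with "a significance level of α = 5%, β = 20% and a power 1–β = 80" per cent. From this, "A sample size of 166 TB patients per arm (332 in total) was calculated".
- Clustering is then allowed for with a design effect of 1.5 at an average cluster size of 50. The resulting requirement reads "we predict that we would require 500 participants, with five clusters in the control arm and five in the intervention arm".
- The last step adds a margin for losses to follow-up: "Accounting for an anticipated 10% dropout rate, we plan to screen and include approximately 547 participants overall".

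The formula is printed below the Figure 1 caption, "where C represents the expected proportion in the control arm and I represents the expected proportion of the intervention arms". The text there adds that each cluster goes on recruiting until it has its required number. The arm-wise sizes are referred to Figure 1, which is not shown in the copy reviewed.

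**The concern.** The same two arms have one planned size in the abstract and another in the section that justifies the size. The abstract's 480 matches no step of the derivation: not the unadjusted 332, not the 498 to 500 after the design effect, not the 547 after dropout, and not the 492 that would remain of 547 after a 10% loss.

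Two things are at stake. First, if 240 per arm is what will be recruited, the trial is smaller than its own calculation requires and the power claim no longer matches it. Second, cluster recruitment stops at a required number. With ten clusters, totals of 480, 500 and 547 correspond to 48, 50 and about 55 per cluster. A reader of the eventual report could not tell whether 480 or 547 enrolled was on target.

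**Working it through.** **Inputs** (Sample size section unless noted): C = 0.50, I = 0.35, difference 0.15; alpha 5%; power 80%; average cluster size 50; design effect 1.5; five clusters per arm; dropout 10%. Arm size of 240 from the abstract. Sidedness is not stated. The two-sided version reproduces 166; the one-sided version gives 131.

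**1. Reproducing the plan's chain**

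S = (1.96 + 0.8416)² × (0.50 × 0.50 + 0.35 × 0.65) / 0.15² = (1.96 + 0.8416)² × 0.4775 / 0.0225 = 166.6 per arm, or 166.4 with 0.84. The plan's 166 is reproduced.

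- Design effect: 332 × 1.5 = 498, about 500 as ten clusters of 50. From the unrounded figure, 166.57 × 1.5 = 249.9 per arm.
- Dropout: 498 × 1.10 = 547.8. The plan's 547 is reproduced.

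The requirement before dropout is therefore 249 to 250 per arm. The abstract's 240 is 9 to 10 per arm lower. The total of 480 is 4% below 500, and 67 (12%) below 547.

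**2. Can 480 be fitted to the chain?**

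- As the number left after dropout: 547 × 0.90 = 492, not 480. Going from 547 to 480 would need a loss of 1 − 480/547 = 12.2%, not 10%.
- As the requirement before dropout: 498 to 500, not 480.

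**3. Power at 240 per arm**

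Power = Φ(0.15 / √(0.4775 / n_eff) − 1.96), where n_eff = analysed per arm / design effect.

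The design effect is either held at 1.5 or recomputed for the smaller cluster. Recomputing needs an intracluster correlation. None is stated, and a design effect of 1.5 at cluster size 50 implies 0.5/49 = 0.0102.

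| Analysed per arm | Design effect | n_eff | Power |
|---|---|---|---|
| 250 | 1.5 | 166.7 | 80.0% |
| 240 (no loss) | 1.5 | 160 | 78.4% |
| 240 (no loss) | 1 + 47 × 0.0102 = 1.48 | 162 | 78.9% |
| 216 (240 less 10%) | 1.5 | 144 | 74.1% |
| 216 (240 less 10%) | 1 + 42.2 × 0.0102 = 1.43 | 151 | 76.0% |

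**4. The dropout step (secondary)**

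To keep N after a 10% loss, enrolment must be N/0.90: 498/0.90 gives 554 (277 per arm) and 500/0.90 gives 556 (278 per arm). Enrolling 547 leaves 492, which is 6 to 8 short of 498 to 500. Power with the design effect at 1.5 is then about 79.4%.

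**The case against.** The strongest reply is that the Sample size section is the operative text and is consistent in itself. The only cluster size it gives is an average of 50, so nothing ties recruitment to the abstract's 240, and the mismatch may be no more than an abstract error. This stands in part: the documents do not show that 240 per arm will govern. It does not remove the contradiction, because the article also gives no reason to disregard the abstract.

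A reader might infer more than the text supports in three ways.

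- **That there are three conflicting totals.** There are not. 500 and 547 are successive steps, the number required and then that number raised for dropout. The conflict is 480 against that pair.
- **That the trial will miss 80% power.** The 74 to 76% holds only if 240 is enrolment before dropout; if 240 are analysed, the shortfall is one to two points. All these figures also belong to the two-proportion formula. The analysis section plans a linear mixed model of the self-efficacy score at three time points under intention to treat. Such a model can use partial data from people who leave, so removing a flat 10% does not describe its power.
- **That 547 is a serious error.** The slip is real, but the plan presents the figure as approximate, and it costs about 0.6 of a power point.

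Figure 1 might explain what 240 represents. It could not make the abstract and the Sample size section agree in their text.

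**Conclusion.** The contradiction between 480 and 500/547 is established from the text alone. By the plan's own formula and design effect, 480 is too small even with complete follow-up.

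The consequence depends on what 240 means: about one to two points of power if it is the number analysed, and about four to six points if it is enrolment before the 10% loss. These sizes assume a two-sided 5% test, 50% against 35%, and the unpooled normal approximation. The 76% figure also assumes an intracluster correlation of 0.0102, inferred from the design effect. The article does not say which meaning of 240 is intended, so a firm statement that the stated power is lost is not supported.

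The numbers must be reconciled, because the article relies on them to justify the trial's size and correcting them is cheap. The dropout inflation is a side note and would not call for a change by itself.

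**What to change.** State one enrolment target, say whether it is before or after dropout, and use it with the matching per-cluster number in the abstract, the Sample size section and Figure 1.

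- **If 240 per arm is the real target:** restate the power as about 78 to 79% if 240 is the number analysed, or about 74 to 76% if 240 is enrolment before the 10% loss, with the intracluster correlation assumed. This changes wording only.
- **If the Sample size section governs:** correct the abstract to match it. At the present 547 this is 67 more than the abstract's 480.
- **While editing, optionally:** replace the multiplication by 1.10 with division by 0.90, giving 554 to 556 (277 to 278 per arm, about 55 to 56 per cluster). That adds 7 to 9 participants relative to 547, but 74 to 76 relative to 480. The cost should be judged against whichever figure recruitment actually follows.
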